## Abstract

Friend and/or family caregivers (FCGs) of those with terminal cancer are heavily relied upon to address the emotional and physical needs of the patient facing death. Although increasing research has focused on testing supportive interventions for FCGs who deliver home-based care at end of life, limited attention has targeted strategies that support grief processing for bereaved FCGs during the months following the patients’ death. Both natural environments and meditation practices are shown to support directed attention, reflection, and the capacity to remain present with painful thoughts and emotions that are essential for grief processing. This mixed-method study assesses the potential of a new tailored online audio nature-meditative intervention to support grief recovery and healing among 70 bereaved cancer caregivers who are in the first year of bereavement. A primary goal is to assess the acceptability and feasibility of both content and delivery methods. Measures for the 6-week intervention include numbers eligible vs. consented; numbers consented vs. completed; number of weeks using the intervention, and self-report feasibility/acceptability. Potential effect size estimate data for future larger scale work will be collected at three time points: baseline (Time 1; study week 0), at the intervention end (Time 2; week 6), and at follow-up (Time 3; study week 12) on quality of life, bereavement (grief), directed attention, anxiety and depressive symptoms. Additionally, semi-structured interviews with a diverse representative subsample of 15 caregivers will be conducted at the end of the 12-week study to further assess acceptability and feasibility in more depth. Data analyses will include descriptive statistics, linear mixed models, and content analysis. Findings will be used to assess and enhance the intervention prior to wider scale testing with the long-term goal of establishing an evidence-based intervention for supporting bereaved cancer caregivers as they process grief and adapt to their loss.

## Introduction

1

The number of patients with advanced cancers who die at home continues to grow in the United States (1). Parallel with this growth is the expanded reliance on friend and/or family caregivers (FCGs) who provide supportive care to patients facing death (2–5). While research evaluating support for cancer FCGs has grown substantively, particularly for FCGs of patients receiving active anti-cancer therapies and for those with advanced cancer at the end of life, comparatively limited research has focused on supporting the bereaved FCG post-patient death (6, 7).

Caring for patients with advanced cancer at the end of life is associated with a high psychological burden (2, 8, 9). FCGs often have limited preparation for the multiple challenges they encounter during the progressive decline in their patient confronting death, often putting personal needs aside as they support the patient during the dying process (10–12). The post-death bereavement period can then be laden with the additional distress associated with confronting the loss of a beloved person, loneliness, and stretches of time that were once consumed with caregiving (13–15). Grief is a painful yet natural and universal human response to loss that usually abates with time (16, 17). However, for those FCGs with poorer mental health, there is heightened risk for complicated grief (17). When not addressed, such grief persists over time, increasing depressive and anxiety symptoms, compromising directed attention and cognitive capacity, and adversely impacting quality of life (QOL) while also increasing risk for morbidity and mortality (6, 13, 16). The recent Diagnostic and Treatment Manual (DSM-5-TR) and International Classification of Diseases (ICD-11) addition of prolonged grief disorder (PGD), characterized by intense anguish and impaired functioning 6 to 12 months and beyond post-loss, confirm the importance of addressing bereavement adaptation early in the post-death period (6, 16–19). Factors associated with increasing complicated grief risk during bereavement include female sex, lower income and education level, comorbid mental and physical health conditions, relationship characteristics, inadequate care provision of the patient at end of life and death circumstances, conflict, and burnout (13, 16).

While the needs of specific individuals facing grief vary, clinical bereavement programs provide services such as informational support, psychoeducation, support groups, brief psychotherapy, pharmacotherapy, and individualized counseling with high levels of variability in types, focus, duration, and outcomes across programs offered (20, 21). Several theoretical perspectives have been adopted that address grief recovery. The dual processing framework identifies grief as a dynamic and adaptive process that oscillates between loss-oriented (acknowledging/processing emotional impact; avoidance and denial) and restoration-oriented (life changes/distraction) coping (22). The stress-coping model frames bereavement as a stressor with problem-focused coping devoted to management of the stressor and emotion-focused coping oriented towards grief processing. Other models include Horowitz’s stress trauma framework which addresses the cognitive intrusions and avoidance that are part of the trauma grief experience and the two-track bereavement model which frame biopsychosocial outcomes and loss transformation as separate tracks in grief recovery (23). A more recent theoretical adaptation integrates the two track and dual processing models (23). Grief focused cognitive-behavioral therapies (GF-CBT), meaning centered therapies, peer support, and integrated therapies that combine acceptance and mindfulness-based therapies with CBT have been evaluated for adults with PGD, and in spousal caregivers with positive impact on grief recovery outcomes (24–30). Both face-face and internet delivered GF-CBT are shown efficacious for depression and grief symptoms associated with PGD (29, 31–33). Gaps, however, remain related to sample homogeneity with limited representation of cultural and racial-ethnically diverse groups, evidence implementation challenges due to financial cost, training needs, and travel needs to on-site venues. Interventions are needed for bereaved FCGs that are readily accessible, convenient, and low cost.

A growing body of evidence supports the benefits of meditation as a mind–body practice that strengthens the capacity to stay present with difficult inner experiences (30, 34–36). Regular meditative practices contribute to changes in functional brain activity in the fronto-parietal regions that directly affect the self-regulatory capacity essential for managing stressors such as the difficulties associated with bereavement (34, 37, 38). With consistency and effort, meditative practices strengthen directed attention, also referred to as the cognitive capacity to focus and concentrate, enhancing present-moment interoceptive awareness of current mental and physical events, and support ‘letting go’ of rumination and worries (34, 38). Importantly, as an evidence-based strategy, research that examines its value in supporting FCGs during the bereavement period is essential.

The natural environment provides a calming space for alleviating distress (39–41). Growing research cites nature’s serene qualities that promote relaxation, help manage stress, and improve emotional well-being (34, 42). Research has also demonstrated that natural environment promotes the restoration of directed attention capacity and thus boost effective cognitive functioning (43, 44). Although the formal testing of nature-based interventions for cancer FCGs is a gap in the science (45), those that have evaluated nature-based interventions in adult populations have identified the aforementioned benefits (46).

The provision of low-cost self-care resources that address bereaved FCGs’ QOL and emotional health post-patient death from cancer is both a critical need and a research gap (6, 10). The present study is novel because it assesses a newly developed nature-based healing meditation (NBHM) intervention that blends meditative practices with nature imagery in an on-line format to promote individualized grief processing among bereaved cancer FCGs. Importantly, on-line delivery of psychotherapeutic interventions have grown with demonstrated efficacy in the past two decades (47). There is growing research that has tested both meditative practices and nature interventions via virtual and online formats (36, 48–51) demonstrating an evidence-base that is complementary given interrelated components such as the ‘meditative qualities and reflection opportunity’ often associated with nature. Thus, combining meditation with exposure to nature as an integrated intervention is posited to yield superior benefits to either alone (52). The six-week technology-mediated intervention described in more detail in the methods section offers auditory guided nature-meditation modules that are anchored in six different natural settings (spring meadow, fall meadow, wooded forest, beach scene, solar system/night sky, evening sky), from which participants may select. Importantly, integration of grief adaptation theory, mechanisms underlying meditative practices that promote mindful awareness, and attention restoration theory provides a conceptual avenue for producing an intervention able to support bereaved FCGs.

The purpose of this paper is to describe the research protocol for assessment of a newly developed nature-based meditation intervention for bereaved FCGs of patients who died from cancer. The research aims include: (1) evaluate the acceptability and feasibility of the content and delivery of the NBHM intervention for use by bereaved cancer FCGs; and (2) assess the potential of the NBHM intervention towards improving parameters of bereavement recovery (see Figure 1).

**Figure 1 fig1:**
[figure not shown]
The conceptual framework whereby the NBHM intervention is theorized to support the bereavement process and enhance QOL as the primary outcome. Potential moderators include sociodemographic characteristics, time since the patients’ death, relationship status, pre-existing health conditions, intensity of grief symptoms, directed attention functioning, and psychological symptoms at baseline. By supporting directed attention, grief processing, and psychological health, the NBHM is posited to promote QOL during a time of great challenge and vulnerability.

## Materials and methods

2

### Study design

2.1

The study uses a single-group, prospective pre-post mixed-methods design to assess the acceptability and feasibility and to estimate effect sizes of the newly developed NBHM intervention on the primary outcome of QOL and secondary outcomes of grief processing (intensity/severity of grief symptoms, directed attention and psychological symptoms). The mixed-method approach will yield important information from both survey and qualitative data regarding the acceptability and feasibility of the NBHM intervention. No comparator is used given the study’s primary aim is to evaluate the feasibility of the new intervention (Figure 2).

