### Sample

2.2

The study sample will consist of adult FCGs. Inclusion criteria are as follows: (1) > 18 years of age; (2) caregiver of a patient who died from cancer during the past one year; (3) able to understand, speak, and read English; (4) able to hear conversation at a normal speaking volume; (5) have a phone and/or an email address where they can be reached; and (6) possess or have access to an internet-connected computer and/or a mobile device capable of displaying web pages. Exclusion criteria are (1) FCGs of persons who died of conditions other than cancer; and (2) FCGs of a patient who died from cancer more than 1 year ago.

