#### Demographic/health characteristics

2.6.1

At baseline (Time 1), a sociodemographic survey will collect information on sex, age, race, ethnicity, education, socioeconomic situation, relationship status, and time since death of the patient from cancer (in months). Information about comorbid conditions as a proxy of FCG health will be assessed using the standardized and validated 21-item Bayliss Comorbidity Index to identify number and types of chronic conditions and their level of interference in daily activities (57).

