#### Power

2.7.1

Consistent with the analytic model (linear mixed-effect model, LMM) for estimating the change in the primary endpoint, QOL, a simulation-based approach (63) to estimate power to detect effect sizes (ESs) ranging from 0.2 (small) to 0.4 (moderate) is used. Because there is no existing literature on the within-participant correlation (
ρ
) of the outcome over time, three scenarios for 
ρ
(0.3, 0.4, 0.5) are used with 1,000 simulations for each of the three ESs (0.2, 0.3, 0.4) and the baseline sample sizes ranging from 40 to 70 for each simulation. For the power of 0.80 and *α* = 0.05, an initial sample size of 42 FCGs is adequate to detect an ES of 0.4 if 
ρ=
0.4 and 55 FCGs are needed if 
ρ=
0.3; 51 FCGs will be adequate to detect an ES of 0.3 if 
ρ=
0.5 and 65 FCGs are needed if 
ρ=
0.4; and more than 70 FCGs will be needed to detect an ES of 0.2 across all scenarios for 
ρ.
 To be conservative and within the budget, and assuming a 20% attrition rate by week 12, a total of 70 FCGs will be recruited.

Basic summary statistics for demographic characteristics and co-morbid conditions in FCG will be calculated. Because the study involves repeated measurements on the same FCG, basic summary statistics will be generated for each of the three time points. All analytic procedures envisioned for this exploratory project are consistent with general best practices, including recommendations made by the National Research Council panel on the prevention and treatment of missing data in clinical trials (64).

Any technology issues that emerge will be meticulously monitored and tracked. To estimate the change in FCGs’ outcomes across time, an LMM for continuous outcomes will be used. The results will be presented in both the original and standardized scales with estimated confidence intervals and no statistical hypothesis testing will be performed. The random effects will account for the correlation/covariance within the FCGs arising from the repeated measurements on each FCG. Further exploratory analyses will be conducted to assess the potential heterogeneity of the longitudinal profile of the outcomes by FCGs’ baseline characteristics (baseline QOL, age, gender, and relationship). Operationally, this heterogeneity will be assessed through interactions between time and any of the FCGs’ baseline characteristics. Estimates from these analyses will provide directional effects for a later larger-scale study.

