## Limitations

4

The study relies on a convenience sample of bereaved FCGs and thus is subject to self-selection bias. Further, the lack of a control group, reliance on self-report measures, and restriction to English speaking participants only also reduce generalizability. As a feasibility and acceptability study, the goal is to assess whether the intervention is usable, satisfactory, and capable of producing promising effect sizes. Further, while the intervention is designed to be low-technology, variations in digital access, personal comfort levels, and adherence may still arise. Strategies such as weekly reminders and optional technical support are intended to buffer this risk. However, given the population digital technology divide (71), the voices of potential FCGs who are technologically less literate or who do not have access to a computer will not be represented in the study (71).

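### Uncontrolled 12-week change is labelled an effect size of the intervention, the missing control group is treated only as a limit on generalizability, and time since death is left off the interaction list

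*Protocol article*

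**What the plan says.** All places are in the protocol article.

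- **Study design (2.1):** the design is single-group and pre-post. One stated purpose is "to estimate effect sizes of the newly developed NBHM intervention on the primary outcome of QOL", with grief, directed attention and psychological symptoms as secondary outcomes. The reason for having no control is given: "No comparator is used given the study’s primary aim is to evaluate the feasibility of the new intervention".
- **Abstract:** outcomes are measured at weeks 0, 6 and 12 and are presented as potential effect-size data for later, larger work.
- **Introduction:** "Grief is a painful yet natural and universal human response to loss that usually abates with time". The same section says that unaddressed complicated grief persists and harms QOL.
- **Sample (2.2):** eligibility covers a "caregiver of a patient who died from cancer during the past one year".
- **Procedures (2.3) and Fidelity (2.5):** staff make weekly contact by email, text or call during weeks 1 to 6.
- **Demographic/health characteristics (2.6.1):** baseline data include "time since death of the patient from cancer (in months").
- **Figure 1 caption:** "Potential moderators include sociodemographic characteristics, time since the" patient's death, along with other baseline factors.
- **Power (2.7.1), which also holds the analysis text:** a linear mixed model estimates change across time, with confidence intervals and no hypothesis tests. Exploratory heterogeneity analyses use interactions of time with "baseline characteristics (baseline QOL, age, gender, and relationship").
- **Limitations (4):** "the lack of a control group, reliance on self-report measures, and restriction to English speaking participants only also reduce generalizability". The same paragraph speaks of the intervention being capable of producing promising effect sizes.

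**The concern.** An effect of an intervention is a contrast with what would have happened without it. This design has no such contrast, and the article itself gives a reason to expect improvement without treatment. A favourable change would therefore be expected even from an inert set of modules, and the wording would present that change as something NBHM produced.

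The one sentence that could warn the reader puts the missing control group under generalizability. Generalizability asks whether a finding carries over to other people. A missing control group raises an earlier question: whether the change is due to the intervention at all. The article does not disclaim attribution anywhere.

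Time since death is the baseline variable most directly tied to natural recovery. It is collected and appears in the conceptual framework, yet the analysis text does not list it. The article would not show whether change is concentrated among the recently bereaved.

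**Working it through.** **1. What the model estimates.** The plan gives no expected change and no rate of natural recovery, so there is no figure of its own to reproduce on this point. The sample sizes in the Power section are not used here, apart from the 70 recruits, the 20% attrition and the range of within-person correlation (rho).

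Expected pre-post change = natural change + effect of weekly staff contact + effect of NBHM.

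One group followed over time identifies the sum only. The part that is not NBHM adds to the reported figure one for one.

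**2. Size of the overstatement (assumed range).** Take natural improvement over 12 weeks as 0.1, 0.2 or 0.3 SD. These values are assumptions. For illustration, a reported change of 0.4 SD (the top of the plan's power grid, not a result) would leave at most 0.3, 0.2 or 0.1 SD for NBHM and staff contact together.

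**3. How often an inert intervention would look promising.**
- Completers at week 12: 70 × 0.80 = 56.
- SE of change in SD units = √(2(1 − rho)/56).
- rho = 0.3: √(1.4/56) = 0.158, so the 95% half-width is 1.96 × 0.158 = 0.31.
- rho = 0.5: √(1.0/56) = 0.134, so the half-width is 0.26.

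| Assumed natural change, NBHM effect zero | Chance that the 95% CI excludes zero (rho 0.3 to 0.5) |
|---|---|
| 0.1 SD | 10% to 12% |
| 0.2 SD | 24% to 32% |
| 0.3 SD | 48% to 61% |

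**4. Time since death across the article.**

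| Place | Time since death |
|---|---|
| Sample (2.2) | may range from 0 to 12 months at entry |
| Demographic/health characteristics (2.6.1) | collected, in months |
| Figure 1 caption | named as a potential moderator |
| Power (2.7.1), list for time interactions | absent |

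**5. What adding it could show.** Suppose months are spread evenly over 0 to 12 (an assumption). Their SD is then 12/√12 = 3.46. The SE of the slope of 12-week change on months is √(2(1 − rho))/(√56 × 3.46), which is 0.046 SD per month at rho 0.3 and 0.039 at rho 0.5. For two people six months apart in bereavement, the 95% half-width for the difference in change is 1.96 × 6 × 0.046 = 0.54 SD, or 1.96 × 6 × 0.039 = 0.46 SD. The term is descriptive and imprecise.

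**The case against.** The best defence is that the design is deliberate and largely disclosed. A single arm suits a feasibility aim. The analysis text correctly describes its target as change across time, forgoes hypothesis tests and calls the project exploratory. The missing control group is listed as a limitation, and the Conclusion foresees a randomised trial. All of this stands, and no control arm is asked for here. It does not cure the label in Study design, and the limitation as worded describes a different problem. A confidence interval around a confounded change is still confounded.

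It can also be said that the interaction list is exploratory and perhaps not exhaustive, since the next sentence speaks of any of the baseline characteristics, and that other Figure 1 moderators are unlisted too. This makes the omission minor. It remains a mismatch that one added term removes.

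The statement on abating concerns grief, while the primary outcome is QOL. The concern is therefore most direct for the PG-13-R and only plausible for QOL, through the Introduction's link between persisting grief and poorer QOL.

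A reader might infer three stronger points, which the documents do not support:

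- **That a later randomised trial will be underpowered.** Nothing says that it will be sized on the raw change. The Abstract and the Power section say only that the estimates will inform later work.
- **That regression to the mean inflates the change.** The Sample section sets no grief, distress or QOL threshold for entry, so selection on a high score is not shown.
- **That the baseline gradient on months since death could be subtracted as a natural-recovery benchmark.** With 70 baselines spread evenly over 12 months, its SE is 1/(√70 × 3.46) = 0.0345 SD per month. Over 12 weeks (2.76 months) that gives ±1.96 × 2.76 × 0.0345 = ±0.19 SD, and about ±0.37 SD if entry spans only 6 months. That is as wide as most of the recovery to be removed. In a self-selected convenience sample the gradient may also be biased.

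**Conclusion.** The point holds as a fault of labelling, disclosure and one omitted covariate. Study design promises an effect of NBHM that a single-group pre-post model cannot deliver. Limitations understates the consequence of having no control group. The interaction list leaves out a moderator that the article names and collects.

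The size cannot be fixed from the documents. If natural recovery over 12 weeks were 0.1 to 0.3 SD, the reported change would overstate any NBHM effect by 0.1 to 0.3 SD, plus whatever weekly contact contributes. That range is an assumption. The single-arm design is acceptable for the feasibility and acceptability aim, which this point does not touch.

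**What to change.** 1. In the Abstract, Study design and Limitations, call the estimate within-person standardised change instead of an effect size of the intervention.
2. In Limitations, say that without a control group the change cannot be attributed to NBHM, and name this as a threat to internal validity, separate from generalizability.
3. State that the pre-post change will not be taken directly as the effect size for a later controlled trial. The outcome SD, within-person correlation and attrition from this study can be used for that planning.
4. Add months since death, with its interaction with time, to the exploratory list in the Power section. Say that it describes how change varies with time since death and does not identify the intervention effect.

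The cost is wording and one covariate already collected. The headline becomes less favourable, and the interaction will be imprecise with 70 participants.
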